Background and rationale	The standard treatment pathway for locally advanced rectal cancer is neoadjuvant chemoradiotherapy (CRT) followed by surgery. Neoadjuvant CRT has been shown to decrease physical fitness, and this decrease is associated with increased post-operative morbidity. Exercise training can stimulate skeletal muscle adaptations such as increased mitochondrial content and improved oxygen uptake capacity, both of which contribute to physical fitness. The aims of the EMPOWER trial are to assess the effects of neoadjuvant CRT and an in-hospital exercise training programme on physical fitness, health-related quality of life (HRQoL), and activity levels, as well as post-operative morbidity and cancer staging.
Comparators	The usual care control group (usual care – no formal exercise training) receive routine care throughout their cancer pathway from diagnosis to surgical resection. No specific advice about exercise training is offered.
Objectives	The aims of this study were to evaluate the following hypotheses:
	Primary hypothesis: A 9-week in-hospital exercise training programme compared with a usual care control group (usual care - no formal exercise training) will result in a clinically significant difference in oxygen uptake at lactate threshold ($$ \overset{\cdotp }{\mathrm{V}}{\mathrm{o}}_2 $$ at $$ {\widehat{\uptheta}}_{\mathrm{L}} $$ ; 2.0 mL.kg^-1.^min^−1^) assessed using CPET, following neoadjuvant CRT prior to elective cancer surgery.
	Secondary hypothesis: a) An in-hospital exercise training programme compared with a usual care control group (usual care - no formal exercise training) will result in an improvement in psychological health benefits assessed using semi-structured interviews and questionnaires such as EORTC QLQ-30 and EQ-5D, following neoadjuvant CRT prior to cancer surgery. b) Neoadjuvant cancer treatment will result in a reduction in $$ \overset{\cdotp }{\mathrm{V}}{\mathrm{o}}_2 $$ at $$ {\widehat{\uptheta}}_{\mathrm{L}} $$ assessed using CPET.
	Exploratory hypotheses: A 9-week in-hospital exercise training programme compared with a usual care control group (usual care - no formal exercise training) will be associated with 1) a change in physical activity, assessed using SenseWear accelerometer, following neoadjuvant CRT prior to cancer surgery; 2) a change in day 5 surgical morbidity (using POMS) and 3) a change in magnetic resonance (MR)-defined local rectal cancer staging assessed using the TNM classification system (tumour, nodes, metastasis) and tumour regression grading (mrTRG).
Trial design	Parallel group randomised controlled multi-centre trial.
Methods: Participants, interventions, and outcomes	
Study setting	In-hospital. Hospitals include: the University Hospital Southampton NHS Foundation Trust; Aintree University Hospitals NHS Foundation Trust; Royal Hampshire County Hospital, South Tees Hospitals NHS Foundation Trust; and Royal Bournemouth Christchurch Hospitals.
Eligibility criteria	Eligibility criteria for inclusion at cancer diagnosis include the following: age ≥18 years, with MR-defined locally advanced (circumferential resection margin threatened) resectable rectal cancer (≥T2N + M0), undergoing standardised neoadjuvant CRT, and with no distant radiological defined metastasis. Exclusion criteria include the following: inability to give informed consent, non-resectable disease, distant metastasis, inability to perform CPET or bicycle exercise, and patients who declined surgery or neoadjuvant CRT, or who received non-standard neoadjuvant CRT.
Interventions	Patients are randomised (1:1) to either an in-hospital exercise training programme or usual care control group following neoadjuvant CRT (week 0).
	Exercise intervention group
	The exercise training programme was designed to improve physical fitness in the time interval between the end of neoadjuvant CRT and surgery. Exercise training begins on the first week following completion of the neoadjuvant CRT with patients exercising in pairs for camaraderie. The exercise training programme is described below.
Outcomes	Following completion of neoadjuvant CRT (week 0) prior to surgery, patients are randomised to an in-hospital exercise-training programme (aerobic interval training for 6 to 9 weeks) or a usual care control group (usual care -no formal exercise training). The primary endpoint is oxygen uptake at lactate threshold ($$ \overset{\cdotp }{\mathrm{V}}{\mathrm{o}}_2 $$ at $$ {\widehat{\uptheta}}_{\mathrm{L}} $$) measured using cardiopulmonary exercise testing assessed over several time points throughout the study. Secondary endpoints include HRQoL, assessed using semi structured interviews and questionnaires, and physical activity levels assessed using activity monitors. Exploratory endpoints include post-operative morbidity, assessed using the Post-Operative Morbidity Survey (POMS), and cancer staging, assessed by using magnetic resonance tumour regression grading.
Participant timeline	CPET is used to assess physical fitness over a series of time points (which vary in each hospital dependent on cancer treatment and time interval between CRT – surgery): baseline (pre-neoadjuvant CRT), mid-chemotherapy-CRT, post-neoadjuvant CRT (week 0), week 3, week 6 and week 9. HRQoL is assessed in two ways: 1) Semi-structured interviews are conducted at week 0 (following neoadjuvant CRT) and at week 6 to 9 (prior to surgery) to explore patients’ perceptions of quality of life, which allows the patients to focus on personal accounts of their HRQoL within a specific context (for example, exercise participation and active cancer treatment); 2) HRQoL questionnaires are administered over several time points during the study: baseline (pre-neoadjuvant CRT), mid-chemotherapy CRT (in UHS only), mid neoadjuvant CRT, post neoadjuvant CRT (week 0), week 3, week 6, week 9 and 30 days post-surgery. Daily physical activity is measured over three consecutive days and nights at a series of time points; baseline (pre neoadjuvant CRT), mid-chemotherapy-CRT (in UHS only), post-neoadjuvant CRT (week 0), week 3, week 6 and week 9. Physical activity is measured using a multi-sensory accelerometer ((SenseWear Pro® armband (Model MF-SW, display model DD100); BodyMedia, Inc., Pittsburgh, PA, USA)) (see Table 1).
Sample size	A sample of 46 patients is required to detect a difference between groups of 2.0 mL.kg^-1.^min^−1^ $$ \overset{\cdotp }{\mathrm{V}}{\mathrm{o}}_2 $$ at $$ {\widehat{\uptheta}}_{\mathrm{L}} $$ using a two-sample t-test at the 5 % significance level with 90 % power. This is based on a standard deviation of the change in $$ \overset{\cdotp }{\mathrm{V}}{\mathrm{o}}_2 $$ at $$ {\widehat{\uptheta}}_{\mathrm{L}} $$ values of 1.8 ml.kg^−1^.min^−1^ and is inflated to allow for 20 % patient drop-out. This estimate was calculated using the sampsi function in Stata/IC 12.0.
Recruitment	If recruitment is not achieving the target sample size, additional hospitals will be opened to recruit participants.
Methods: Assignment of interventions	
Allocation:	
Sequence generation	Patients are randomised (1:1) to either an in-hospital exercise training programme or usual care control group using the Trans European Network for patient randomisation in clinical trials system (TENAELA System).
Implementation	Randomisation will be generated by the research nurse/Physiologist at each hospital site.
Blinding	Two independent physiological data assessors are blind to group allocation and are independent to the intervention.
Methods: Data collection, management, and analysis	
Data collection methods	For the primary and secondary outcomes, CPET measures changes in physical fitness. Questionnaires and semi-structured interviews will assess changes in HRQoL and physical activity monitoring measures changes in activity levels. Other outcomes are listed in Table 1: Outcomes and assessment measures used in the EMPOWER trial.
Data management	Data will be double data entered, and data validation will take place according to the procedures set out in the data management plan and data validation plan. Prior to any statistical analysis, all variables will be checked for number of missing values, impossible and improbable values. Impossible and improbable values will be defined by clinical opinion. Improbable values will also include values that are outside three standard deviations of the mean value. Any questions regarding the data will go back to the data manager. Descriptive statistics will be calculated for all variables and distributional assumptions checked.
Statistical methods	The effect of neoadjuvant CRT and the exercise intervention on physical fitness will be assessed using a two-sample t-test, and a 95 % confidence interval on the mean difference between the two groups will be presented. In order to assess the sensitivity of results to covariates, a further ‘adjusted’ effect will be calculated using linear regression where up to three candidate covariates will be identified. Basic exploratory analysis of physical fitness at each time-point will be undertaken to investigate the longitudinal response of fitness. Linear mixed modelling will then be employed to compare more formally the fitness at each time-point. Confirmatory analysis using ordinal regression will be used to assess the suitability of the t-test for comparing HRQoL between groups. The effect of an in-hospital exercise training programme on physical activity will be analysed in the same way as physical fitness. The presence/absence of post-operative morbidity as defined by a POMS score > 0 will be compared between groups by calculating the relative risk with a 95 % confidence interval. Cancer staging will be reported as tumour, node metastasis version 5 (TNM) staging, Response Evaluation Criteria in Solid Tumours (RECIST) and MR tumour regression grading (mrTRG) criteria. Pathological outcomes will be graded according to the pathological tumour regression grading (TRG) and TNM). Univariate logistic regression analysis will be used to analyse the association between demographic variables (patient age and sex), MRI parameters and pathologic tumour response This enabled calculation of odds ratios (OR) for the probability of an unfavourable pathological outcome. Analyses of sensitivity, specificity, positive and negative likelihood ratios will be performed.
Methods: Monitoring	
Data monitoring	Data is monitored after the first complete patient at each site to ensure high quality data. Additionally, quality checks are carried out on all CPET’s. An interim analysis will be conducted at the half-way point of the trial.
Harms	All adverse events are recorded in the relevant case report form; adverse events during CPET are reported to the chief investigator and adverse effects during exercise training (pain and muscle soreness) are recorded in the relevant case report form by the research physiologist/nurse. Fatal or life-threatening serious adverse events (SAEs) are reported within 24 hours of the local site becoming aware of the event. The SAE form documents the nature of the event, date of onset, severity, corrective therapies given, outcome and causality (that is, unrelated, unlikely, possibly, probably, definitely). Any questions concerning adverse event reporting are directed to the chief investigator in the first instance.
Ethics and dissemination	
Research ethics approval	Ethical approval: North West Centre for Research Ethics Committees (13/NW/0259, Date: May 2013)
Protocol amendments	Protocol amendments will be agreed and approved by the North West Centre for Research Ethics Committees.
Consent or assent	All potentially eligible patients are identified at multi-disciplinary meetings and approached with written information about the trial at the oncology/surgical outpatient appointment. Patients are contacted by telephone to provide additional information about the trial and to confirm their eligibility. If the patient chooses to participate in this trial, the first research visit is organised where written informed consent is obtained and all baseline measurements are undertaken.
Confidentiality	Data will be entered with all direct patient identifiers removed, patients will be identified by study codes. All physiological data are held in an encrypted format. All data will be stored in a secured locked room.
Declaration of interests	The authors declare that they have no competing interests.
Access to data	Only members of the clinical and research team will have access to patient records.
Dissemination policy	Dissemination of findings to the academic community will be led by the lead applicant guided by the SMG. Dissemination of research findings to patients and the general public will be led by the patient representatives guided by the SMG. The SMG will give public engagement interviews/talks in support of the patient representatives. Active patient involvement will be sought for radio and television interviews, together with issuing of patient statements that can be used at local hospital level to raise awareness regarding prehabilitation and an active life-style in general. The SMG have extensive experience of disseminating medical information to the public and the media, due to the involvement of [name] as founder member of the Improving Surgical Outcomes Group. He is also involved in the Caudwell Xtreme Everest project, which was widely publicised. The group delivered more than 100 lectures to schools, colleges and in other public forums.

## Discussion

The cancer treatment pathway for locally advanced rectal cancer carries some risk. Neoadjuvant CRT and surgery are associated with side effects and post-operative complications [1, 31]. The level of risk associated with surgery has been examined in a recent European Surgical Outcome Study [32], which reported a mortality rate (3.6 %) that was substantially higher than expected. In the United Kingdom, interest is growing in the use of CPET to objectively risk stratify fitness prior to major surgery in order to better inform a discussion of risk within the collaborative decision making process and to aid personalised perioperative patient care [33]. Physical fitness is an important element of post-operative outcome, and exercise training has the ability to improve clinically important CPET variables [34]. The EMPOWER trial will be the first RCT to investigate the effects of neoadjuvant CRT and an in-hospital exercise training programme on physical fitness, HRQoL and physical activity, as well as post-operative morbidity and cancer staging.

Pre-operative physical fitness is associated with post-operative outcome, with the less fit patients having a greater prevalence of adverse outcomes. Neoadjuvant CRT decreases physical fitness in this patient group, and this decrease is associated with increased post-operative complications [10]. The EMPOWER trial will evaluate the effect of the intervention on physical fitness, HRQoL, physical activity and positive behavioural responses to exercise in the short term. Additionally, the EMPOWER intervention has the potential to effect a long-term benefit because an improvement in perioperative fitness might translate into better post-operative outcomes (longer survival and fewer post-operative complications), cancer down-staging and less demand on hospital resources (reduction in patient length of stay, reduced demand for post-operative high dependency care and associated health economic benefits). The EMPOWER trial will also yield an effect size which can be used to power a further definitive randomised controlled trial and to investigate the association of change in pre-operative physical fitness with exercise and post-operative complications.

Strengths of the EMPOWER trial include the study design with parallel group 1:1 randomisation; the two independent physiological data assessors who are blind to group allocation and independent of the intervention; and that the multi-disciplinary team caring for the patients are not provided with any information regarding predictive measures (for example, CPET variables) ensuring a low risk of confounding by indication [35]. Also, patients are recruited consecutively, all of whom are scheduled for a pre-defined CRT regime and have a homogenous MR-defined rectal cancer staging. Furthermore, the statisticians conducting the analyses are blind to the group allocation until after the analysis is complete. Data are handled using a double entry data system, and impossible or improbable values are questioned. The novelty of the in-hospital exercise training programme in this patient cohort and the statistical analyses used are also worth highlighting.

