## Abstract

**Background:**

The standard treatment pathway for locally advanced rectal cancer is neoadjuvant chemoradiotherapy (CRT) followed by surgery. Neoadjuvant CRT has been shown to decrease physical fitness, and this decrease is associated with increased post-operative morbidity. Exercise training can stimulate skeletal muscle adaptations such as increased mitochondrial content and improved oxygen uptake capacity, both of which are contributors to physical fitness. The aims of the EMPOWER trial are to assess the effects of neoadjuvant CRT and an in-hospital exercise training programme on physical fitness, health-related quality of life (HRQoL), and physical activity levels, as well as post-operative morbidity and cancer staging.

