## Background

The standard treatment pathway for magnetic resonance (MR)-defined, locally advanced rectal cancer is neoadjuvant chemoradiotherapy (CRT) followed by total mesorectal excision surgery [1, 2]. Chemotherapy, combined with radiotherapy, improves local disease control and local recurrence for locally advanced rectal cancer [3–5]. With optimised local treatment, including neoadjuvant CRT and surgery, local relapse rates have now been reduced to less than 10 % [2]. Cancer is associated with cachexia, which, in the pre-operative period, has been shown to influence perioperative outcome, increasing the risk of complications, mortality and length of hospital stay in major gastrointestinal surgery [6]. Chemotherapy has been related to skeletal muscle wasting, oxidative stress, mitochondrial death [7] and reduced *in vivo* mitochondrial function [8]. Furthermore, cancer treatment has been linked to decreased physical fitness levels, which appear to be related to the type of treatment; that is, physical fitness is lower in those receiving surgery and radiotherapy in combination with chemotherapy than in those who receive radiotherapy or surgery alone [9]. Neoadjuvant CRT has been shown to be associated with a decrease in objectively measured physical fitness, as measured by cardiopulmonary exercise testing (CPET) in those with locally advanced rectal cancer [10]. This decrease in physical fitness was in turn shown to be associated with increased short-term post-operative morbidity [10]. Moreover, a decrease in physical fitness has also been shown in a group of upper gastrointestinal cancer patients following neoadjuvant chemotherapy [11]. In this case, the change was associated with 1-year mortality [11].

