### Secondary hypothesis

An in-hospital exercise training programme compared with a usual care control group (usual care; no formal exercise training) will result in an improvement in psychological health benefits as assessed using semi-structured interviews and questionnaires such as the EORTC QLQ-30 and EQ-5D following neoadjuvant CRT prior to cancer surgery.Neoadjuvant CRT will result in a reduction in $$ \overset{\cdotp }{\mathrm{V}}{\mathrm{o}}_2 $$ at $$ {\widehat{\uptheta}}_{\mathrm{L}} $$ as assessed using CPET.

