### Participants

Eligibility criteria for inclusion at cancer diagnosis include the following: age ≥ 18 years, with MR-defined, locally advanced (circumferential resection margin threatened), resectable rectal cancer (≥ T2N + M0), undergoing standardised neoadjuvant CRT; with no distant radiological defined metastasis. Exclusion criteria include the following: inability to give informed consent, non-resectable disease, distant metastasis, inability to perform CPET or bicycle exercise, and patients who declined surgery or neoadjuvant CRT or who received non-standard neoadjuvant CRT. Figure 1 provides an algorithm of the clinical pathway and the complete series of assessments for the duration of the trial.

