### Recruitment and randomisation

The EMPOWER trial is currently recruiting (start date is August 2013; end date is December 2015). All potentially eligible patients are being identified at multi-disciplinary meetings and approached with written information about the trial at the oncology/surgical outpatient appointment. Patients are contacted by telephone to provide additional information about the trial and to confirm their eligibility. If the patient chooses to participate in this trial, the first research visit is organised where written informed consent is obtained and all baseline measurements are undertaken. Following neoadjuvant CRT (week 0), patients are allocated to the in-hospital exercise training group or usual care control group. Patients are randomised (1:1) to either an in-hospital exercise training programme or usual care control group using the Trans European Network for patient randomisation in clinical trials system (TENAELA System).

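### The article presents chemoradiotherapy (CRT) effects as something this RCT assesses, but the design yields only uncontrolled change over the CRT period, which the named two-sample t-test cannot estimate

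*Protocol article*

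**What the plan says.** The Abstract gives the aims as "to assess the effects of neoadjuvant CRT and an in-hospital exercise training programme on physical fitness", and the sentence goes on to quality of life, activity, morbidity and staging. The Background and rationale row of Table 2 (SPIRIT) repeats it. The Discussion attaches the same list to the randomised design: the trial "will be the first RCT to investigate the effects of neoadjuvant CRT and an in-hospital exercise training programme on physical fitness".

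One formal hypothesis concerns CRT. Under Secondary hypothesis it begins "Neoadjuvant CRT will result in a reduction in" and refers to oxygen uptake at lactate threshold. The matching item (b) in Table 2 names neoadjuvant cancer treatment as the exposure instead of CRT.

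The design is clear. Recruitment and randomisation states: "Following neoadjuvant CRT (week 0), patients are allocated to the in-hospital exercise training group or usual care control group". The exclusions under Participants cover "patients who declined surgery or neoadjuvant CRT or who received non-standard neoadjuvant CRT", and the Discussion describes the patients as "all of whom are scheduled for a pre-defined CRT regime".

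Statistical analyses, and the Statistical methods row of Table 2, name a single two-sample t-test for the effects of both CRT and exercise on fitness. A linear mixed model across time points follows.

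**The concern.** Two exposures are named in one aim, and only one of them is randomised. A reader who takes the Discussion sentence at its word would give any reported CRT effect the standing of a randomised result. No patient goes without CRT, so every statement about it has to come from comparing patients with themselves before and after.

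The article gives reasons why that comparison is not clean. The Background says "Cancer is associated with cachexia, which, in the pre-operative period, has been shown to influence perioperative outcome", so fitness may change with the disease itself. Baseline measurements are taken at the first research visit, so week 0 is a repeat CPET. At UHS some patients have four cycles of chemotherapy before CRT.

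At stake is what the trial may conclude about CRT. The exercise comparison is not touched.

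**Working it through.** **1. The plan's own figure.** The sample size is the only design figure, and it concerns exercise. Inputs from Sample size calculation: difference 2.0 and SD of change 1.8 mL/kg/min, 5% level (two-sided assumed), 90% power, 20% drop-out.

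- n per arm = 2 × [1.8 × (1.9600 + 1.2816) / 2.0]² = 17.02, rounded up to 18
- 18 / (1 − 0.20) = 22.5, rounded up to 23 per arm, so 46 in total

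The stated 46 reproduces (noncentral-t power at 18 per arm is 0.899). It says nothing about CRT.

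**2. What each outcome can show about CRT** (Table 1 and the outcome sections).

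| Outcome | Pre-CRT value | Value after CRT, before training | Later values | Information on CRT |
|---|---|---|---|---|
| Oxygen uptake at lactate threshold | yes | week 0 | weeks 3, 6, 9 | uncontrolled change, all patients |
| HRQoL questionnaires | yes | week 0 | weeks 3, 6, 9 and after surgery | uncontrolled change, all patients |
| Physical activity | yes | week 0 | weeks 3, 6, 9 | uncontrolled change, all patients |
| Staging by imaging | yes | none | week 9 | CRT plus nine further weeks, plus training in one arm |
| POMS | none | none | days 3, 5, 8, 15 after surgery | none: no pre-CRT value and no CRT-free patient |

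**3. The named test.** Let D be a patient's week 0 value minus the pre-CRT value, with mean γ. Randomisation comes after week 0, so both arms share the same γ. The expected two-sample difference in D is γ − γ = 0, whatever γ is. Applied to change after week 0, the same test estimates the exercise effect only. Neither use estimates γ. The mean of D over all patients does, and so can the mixed model.

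**4. What γ contains.** γ = CRT effect + disease course and elapsed time + repeat-test effect + (some UHS patients) prior chemotherapy. Without a CRT-free comparator the terms cannot be separated. Whatever the other terms add up to enters the estimate one for one, and a larger sample does not reduce it. For the UHS chemotherapy patients, the extra visit between chemotherapy and CRT allows a later starting point, but any carry-over from the chemotherapy remains.

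**5. Is γ estimable with useful precision?** The 95% CI half-width is t × SD / √N. The SD of the CRT-period change is not given. Borrowing 1.8 is an assumption.

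- N = 46: 2.014 × 1.8 / √46 = 0.53 mL/kg/min
- N = 36 (18 per arm): 2.030 × 1.8 / √36 = 0.61
- SD from 1.5 to 2.5: 0.45 to 0.74 with 46 patients, 0.51 to 0.85 with 36

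The change can be estimated usefully. Its interval reflects sampling error only and none of the bias in step 4.

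**The case against.** The best reply is that the CRT wording is a one-line summary and should not be read word by word. The Aims section says the aims are to evaluate the listed hypotheses, and only one of these concerns CRT, for oxygen uptake at lactate threshold. Morbidity and staging are hypothesised for exercise versus usual care, and POMS is compared between groups. The Abstract and the end of the Background tie the first-RCT claim to the exercise intervention, and randomisation after CRT is stated openly. Nothing says that the baseline to week 0 change will be reported as a randomised effect.

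Most of this stands. A reader might infer that the CRT aim fails for all five outcome areas. The documents do not support that: fitness, HRQoL and activity have values on both sides of CRT, and staging has pre-CRT and week 9 scans. Nor do they show a plan to estimate a CRT effect on morbidity. The Background says that cancer is associated with cachexia, not that it causes it, and gives no rate of fitness loss over the CRT weeks.

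The reply leaves three things unanswered: the Discussion sentence does place CRT under the RCT label, the secondary hypothesis is causal, and the analysis section names a between-arm test for the CRT effect. These are statements in the article, not details left to a fuller document, and no analysis plan could supply a CRT-free comparator.

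**Conclusion.** The point holds in limited form. The wording gives CRT effects a randomised standing that the design cannot provide, and the t-test named for them cannot estimate them.

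- **Morbidity:** a CRT effect is not estimable, although no formal hypothesis requires it.
- **Fitness, HRQoL and activity:** change over the CRT period is estimable but cannot be attributed to CRT.
- **Staging:** the available change is further mixed with nine weeks of follow-up and, in one arm, training.

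The size of the misattribution cannot be stated, because the documents give no figure for background drift or repeat-test effect. It would also be tempting to scale it against 2.0 mL/kg/min, but that figure is the between-group exercise difference and not a benchmark for change over CRT. The half-widths shown rest on an assumed SD and only illustrate that the change can be estimated.

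The randomised comparison, its sample size and the primary endpoint are unaffected.

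**What to change.** - In the Abstract, the Background and rationale row of Table 2, and the Discussion, limit the randomised aim and the first-RCT claim to exercise versus usual care. Drop CRT as an exposure for morbidity.
- Restate the CRT hypothesis identically under Secondary hypothesis and in item (b) of Table 2: within-patient change in oxygen uptake at lactate threshold from pre-CRT to week 0, in all patients. State which pre-CRT visit starts the interval for UHS patients who had chemotherapy first.
- In Statistical analyses and the Statistical methods row of Table 2, keep the two-sample t-test for exercise only. Estimate the CRT-period change by a paired or mixed-model analysis with a 95% CI, reported as uncontrolled change and not as an effect caused by CRT.
- Report any HRQoL, activity or staging change in the same descriptive way, noting for staging the longer interval and the training in one arm.

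The cost is wording and one analysis on data already scheduled, with no new visits or patients. The downside is a weaker claim about CRT.
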